### Experimental procedure

The intervention was carried out twice a week, on alternate days, spanning a total duration of 16 weeks. To enhance communication and enable active participation in meetings, promoting conversational dynamics and practical engagement, the IG participants were divided into two groups. The sessions, lasting approximately one and a half hours, were conducted both in person (80%) and online (20%), using the Google Meet platform. All meetings were based on the Self-Determination Theory and involved activities conducted by professionals in the field of Physical Education, affiliated with UFSC, along with the participation of external guests. These professionals were tasked, through the proposed dynamics, to support the basic psychological needs of the participants. This influence on the quality of motivation for behaviors and the level of participation/involvement in these behaviors has the potential to bring about changes in mental and physical health outcomes. In all meetings, professionals sought to implement the classification system of techniques constituting interventions based on Self-Determination Theory, as developed by Teixeira et al. [36]. The organizing principle of this system revolves around the satisfaction of psychological needs within healthcare contexts. According to the authors, each technique targeted the construct most closely related to psychological need satisfaction (autonomy, competence, or relatedness), with the aim of achieving a heightened level of motivation and promoting behavior change. In Fig. 2, it is possible to visualize the basic process model of the Self-Determination Theory that was developed in the intervention program.

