### Sample size, randomization, and allocation concealment

The sample size was calculated using G*power 3.1.9.2 software, and was based on an ANOVA model for repeated measures with three time points and two groups. Parameters included an average effect size of 0.25, statistical power of 80%, and 5% significance level for two-tailed tests, reaching a value of 28 individuals. Anticipating a potential dropout rate of up to 50%, the number calculated was doubled, bringing the total sample size to 56 individuals. Eligible individuals were randomly assigned to either the control group (CG), instructed to maintain their usual activities, or the intervention group (IG), which actively participated in the program. To ensure numerical and participant characteristic balance between groups, randomization was stratified by sex, age, and PHQ-9 score, employing a 1:1 ratio. The randomization process was executed using the online platform randomizar.org by researchers not directly involved in the intervention. The allocation list was concealed from all study evaluators.

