The main activities included (a) lectures covering various topics focused on the adoption and maintenance of healthy habits; (b) distribution of educational materials, including instruction manuals, addressing the necessary care individuals should take in their daily lives; (c) group discussions aimed at exploring the development and progress of the intervention; (d) practical activities involving the participation of family and friends; and (e) practical classes, such as yoga, capoeira, exergames, cycling, walking with pets, weight training, functional training, and gymnastics. The meetings followed a schedule with specific dates, times, and content, divided into four blocks, each consisting of eight sessions. The blocks were organized as follows: (a) contextualization, involving moments for the group to better acquaint themselves and dynamic activities addressing topics such as the relationship between depressive symptoms and 24-h movement behaviors; (b) adherence, providing general and specific guidelines on 24-h movement behaviors; (c) experimentation, offering participants more opportunities to engage in physical activity in different contexts and situations; and (d) maintenance, focusing on strategies and tools for maintaining healthy behaviors in both the short and long term.

Face-to-face meetings were conducted at the onset of each block, which represented 4 weeks of intervention, in order to establish a connection among participants and fostering discussions about their experiences during these periods. The face-to-face meetings took place at the premises of the Federal University of Santa Catarina and at locations suitable for engaging in physical activities. The remaining sessions were conducted via an online meeting platform. A WhatsApp group was also created to address inquiries, distribute support materials, and share photos, audios, and/or other resources related to the proposed activities, addressing other demands that emerged throughout the program. Tables 1, 2, 3, and 4 present the themes, objectives, support techniques for basic psychological needs, and the approaches/actions implemented in each meeting throughout the program, with each table corresponding to 1 month (4 weeks of intervention). In the supplementary material, it is possible to check the lesson plans for all 32 meetings of the Vincular Project, providing detailed information about the proposed content and dynamics.

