Meeting 9: Conducting the intervention □ [1]	To discuss the experiences of the first month	- "Knot dynamics". The participants stand in a circle and memorize who is on their left and right side. To the sound of music, they walk freely around the room. When the teacher asks them to, they must stop where they are and hold hands with the people next to them, but without moving. The aim is to undo the knot and return to the starting position	- Fill in a list of routine activities in order to assess how they can better optimize their time and adopt new healthy behaviors in the short and long term	Competence: barriers acknowledge Relatedness: social support	- Recognizing the stages for behavior chances of each participant - Encouraging the group`s cohesion in the activities and resolution of problems
Meeting 10: Tools for 24-h movement patterns ○ [2–5]	To provide information on resources that help promote physical activity, reduce sedentary behavior and improve sleep quality	- Practicing physical activity and meditation through YouTube channels	- Choose two apps or another tool, try them out and report back on the experience. If possible, invite someone to practice together	Autonomy: provision of choice Relatedness: social support	- Favoring that the participant has and perceives option of choice in the conduction of all stages relative to the program of physical activity - Encouraging the participant to invite friends and Family to carry out/participant in the programs of physical activity
Meeting 11: *Exergames* □ [6–8]	To provide and explore a new tool for practicing physical activity, using all the elements of the body culture of movement	- Practice with Xbox 360: Just Dance, Kinect Sports	-	Relatedness: involvement and connection	- Engaging actively in activities, including doing and playing together

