Meeting 32: Project closing: trail □ [15–17]	To provide moments of reflection on the trajectory of the intervention and future prospects	Trail on the Costa da Lagoa (Florianópolis/SC)	- Send a statement about your experience with the project, with your perceptions of the issues addressed in the intervention	Autonomy: orientation with intrinsic objective Competence: provision of encouragement and support Relatedness: cooperation group	- Rationalizing the role of physical activity for reasons such as building a sense of friendship, improvement of skills, energy gain, and a better lifestyle - providing positive feedback to the class and individually, whether recognizing an effort of the participant or complimenting his attitude - Creating groups in virtual environments for experience exchange, facilitating the communication between participants

□: face-to-face meetings; ○: online meetings; 1: Gillison et al. [37]; 2: Brooks et al. [97]; 3: Friedman; Krause-Parello [98]; 4: Kamioka et al. [99]; 5: Nahas [55]; 6: Conn et al. [100]; 7: Laux et al. [101]; 8: Serra; Pimenta; Quemelo [102]; 9: Ekinci; Sanlier [103]; 10: Kris-Etherton et al. [104]; 11: Singh et al. [105]; 12: Bento-Soares; Schiavon [106]; 13: Menegaldo; Bortoleto; Mateu [107]; 14: Menegaldo; Bortoleto [108]; 15: Brito et al. [93]; 16: Coventry et al. [94﻿]; 17: Frühauf et al. [95]

The GC, in turn, was expected to continue with its usual activities. However, recognizing the high chance of participants allocated to this group dropping out the research, a decision was made to maintain contact through telephone messages every 2 weeks. The content of these messages included psychoeducational materials on mental health, as well as guidelines for practicing physical activity, reducing sedentary behavior, and improving sleep, which were also shared with individuals who did not meet the eligibility criteria, as mentioned previously (Table 5). It is also worth noting that, if the effectiveness of the intervention is confirmed, the researchers plan to offer the intervention to the control group later, with the goal of extending benefits to all study participants.

**Table 5 Tab5:** Support materials provided to control group participants

Materials	Description	Access

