To verify the effect of the intervention on the primary outcome and secondary outcomes, per-protocol and intention-to-treat analyses will be conducted. The first one will take into account only IG participants who followed the activities until the last meeting, complied with the planned intervention protocol with at least 50% overall attendance and in each of the four blocks of the intervention, in addition to being duly evaluated in the line moments baseline and post-intervention. This decision aligns with the intervention proposal, in which the initial meetings comprised more theoretical activities, with practical sessions beginning in the second month onwards. Those from the GC who participated in the assessments will also be considered. The second analysis will include all individuals from the CG who participated in both data collections, and those from the IG considered in the per-protocol analyses. To fill in the missing data from the other participants, the multiple imputation technique will be applied, using sex, age, and the variables of interest as predictors. For comparisons between periods (pre- and post-intervention) and between groups (intervention and control), analysis will be conducted using generalized estimating equations (GEE), with Bonferroni post hoc adjustments. The significance threshold will be set at *p* ≤ 0.05. However, for time*group interactions, *p* ≤ 0.10 will be considered marginally significant [126]. Additionally, effect sizes will be calculated based on (a) Cohen’s d [127], considering small values (0.20 ≤ d < 0.50), medium values (0.50 ≤ d < 0.80), and large (d ≥ 0.80); and (b) partial eta squared (ηp2), with small (0.02 ≤ ηp2 < 0.13), medium (0.13 ≤ ηp2 < 0.26), and large (ηp2 ≥ 0.26) effect sizes [128]. These procedures will be performed using the Statistical Package for the Social Sciences (SPSS, version 23.0) software.

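### The intervention arm is delivered in two groups and controls individually, but neither the sample size nor the described GEE allows for correlation within a delivery group

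*Protocol article*

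**What the plan says.** **Randomization.** Sample size, randomization, and allocation concealment describes 1:1 allocation of individuals.

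**Intervention arm.** Experimental procedure states that "the IG participants were divided into two groups", with two meetings a week for 16 weeks, 32 in all. Interaction between participants is part of the design. The activities include "group discussions aimed at exploring the development and progress of the intervention". The face-to-face meetings that open each block are held "in order to establish a connection among participants". Table 2 (Meeting 9) lists the strategy "Encouraging the group`s cohesion in the activities and resolution of problems".

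**Control arm.** Controls continue their usual activities without group sessions. To limit dropout, "a decision was made to maintain contact through telephone messages every 2 weeks".

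**Sample size.** It rests on "an ANOVA model for repeated measures with three time points and two groups", gives 28, and is doubled to 56 for up to 50% dropout.

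**Analysis.** Under Data treatment and statistical analyses, for periods and for the two arms, "analysis will be conducted using generalized estimating equations (GEE), with Bonferroni post hoc adjustments". The imputation predictors are sex, age and the variables of interest. The delivery group is not mentioned in the sample size, the GEE, the imputation, the mediation models or the limitations in the Discussion.

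**The concern.** This is a partially nested design: one arm is clustered in delivery groups and the other is not. People who spend 16 weeks in the same sessions with the same peers may end with outcomes more alike than those of people in different groups. Here that likeness is close to an intended mechanism. Relatedness is both a secondary outcome and a proposed mediator, and the sessions are built to foster it.

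If the correlation is positive, the mean of the intervention arm varies more than a model of independent individuals allows. Confidence intervals are then too narrow and the 5% test rejects too often. Small-sample corrections to a GEE clustered on person do not address this. With only two groups, a favourable group dynamic is also hard to tell apart from an effect of the programme. That matters because the Discussion hopes the results will inform public policy, which means generalizing beyond these two groups.

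**Working it through.** **1. Reproduce the plan's figure.** Inputs from the sample-size section: f = 0.25, two arms, T = 3 time points, two-sided 5%, power 80%. The article gives neither the correlation between repeated measures nor the sphericity correction, so ρ = 0.5 and ε = 1 are assumed. For the within-between interaction:

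- λ = f² × N × T / (1 − ρ) = 0.0625 × 28 × 3 / 0.5 = 10.5
- df1 = (2 − 1)(3 − 1) = 2; df2 = (28 − 2)(3 − 1) = 52
- power = 0.812, and N = 28 is the smallest even total reaching 80%
- 28 / (1 − 0.5) = 56

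The stated 28 and 56 reproduce exactly for independent individuals, so they contain no design effect.

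**2. Group sizes.** Two groups in the intervention arm, equal split assumed. With all 56 retained: 28 v 28, m = 14 per group. With 50% dropout, equal between arms: 14 v 14, m = 7 per group.

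**3. Standard error.** Clustering affects one arm only. With equal arms and equal total variance:

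- design effect in the intervention arm: DE = 1 + (m − 1) × ICC
- ratio of true to unadjusted standard error: √((DE + 1) / 2)
- type I error at nominal 5%: 2 × (1 − Φ(1.96 / ratio))

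The ICC is that of the analysed quantity (change in the outcome). The article gives none, so 0.02 to 0.10 is an assumption.

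| Arms | ICC | DE | SE ratio | Type I error, formula | Type I error, simulation |
|---|---|---|---|---|---|
| 14 v 14 | 0.02 | 1.12 | 1.03 | 5.7% | 5.7% |
| 14 v 14 | 0.05 | 1.30 | 1.07 | 6.8% | 6.8% |
| 14 v 14 | 0.10 | 1.60 | 1.14 | 8.6% | 8.6% |
| 28 v 28 | 0.02 | 1.26 | 1.06 | 6.5% | 6.6% |
| 28 v 28 | 0.05 | 1.65 | 1.15 | 8.9% | 8.8% |
| 28 v 28 | 0.10 | 2.30 | 1.28 | 12.7% | 12.9% |

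Worked row (14 v 14, ICC 0.05): DE = 1 + 6 × 0.05 = 1.30; √(2.30 / 2) = 1.072; 1.96 / 1.072 = 1.828; error 6.8%.

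The simulation used 200,000 runs per cell under no effect, with a random group effect in the intervention arm, independent controls and an ordinary two-sample t-test on change.

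**4. The 10% label.** The plan calls time-by-group interactions marginally significant at p ≤ 0.10. At ICC 0.05 the same formula, with 1.645 in place of 1.96, gives about 12.5% (14 v 14) or 15.3% (28 v 28).

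**5. Power.** Dividing N by (DE + 1) / 2 in step 1, interaction power at 14 v 14 falls from 81% to about 79%, 75% and 69% for ICC 0.02, 0.05 and 0.10. At 28 v 28 it stays at about 97%, 95% and 89%. Interval width and type I error are the main issue; power suffers only after heavy dropout.

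**The case against.** The strongest reply is that the article says little about the groups. Several readings that a reader might infer are not supported.

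- **Closed groups.** The text says only that participants were divided. It does not say that membership was fixed or that every meeting was held separately. One WhatsApp group is described for the programme, and events such as the closing trail are not described as run twice. Contact across the groups would lower the between-group variance.
- **Different leaders or timetables.** The sessions are "activities conducted by professionals in the field of Physical Education", plus guests, and nobody is assigned to one group. If the same people led both, their influence is common to the whole arm, adds no between-group variance, and lies outside this correction.
- **A GEE shown to cluster on person only.** The article names no subject variable, cluster level or working correlation, and a full protocol or analysis plan may do so.
- **Certain harm.** The excess error exists only if the ICC is above zero. At ICC 0.01 with 14 per group the error is about 5.7%.
- **The largest figures.** An error near 13% and a standard error 28% larger need both ICC 0.10 and no dropout, whereas the plan allows for losing half the sample. The simulation is also a t-test on change, not the planned GEE.

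All of this stands as a limit on the claim. It does not remove the point. Shared sessions and peers are enough to make within-group correlation plausible, with no need for closed groups or separate leaders. Nor is it merely a detail left to another document: the article fixes the sample-size model, the comparison, the imputation predictors and the thresholds, and none of them allows for a feature of its own design.

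**Conclusion.** The point holds in conditional form. The intervention arm is nested in two delivery groups, controls are not, and nothing in the article allows for it. If outcomes are positively correlated within delivery group, the planned standard error is too small and the type I error exceeds 5%.

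The 14 v 14 figures matter most, since that is the size on which the trial was powered: a standard error about 3%, 7% or 14% larger than reported. At full retention it would be about 6%, 15% or 28% larger. These figures rest on an assumed ICC of 0.02 to 0.10, equal group sizes, equal dropout between arms and equal total variance. The article does not show that the error rate is in fact inflated, or by how much. Two groups cannot estimate the ICC, so the trial's own data will not settle it. The point merits a sensitivity analysis and a stated limitation; it does not invalidate the trial.

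**What to change.** The trial is concluded, so the number of groups cannot change, but the analyses are still written as future work. Four additions would suffice:

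1. Keep the delivery-group identifier in the analysis dataset.
2. Report PHQ-9 change separately for the two delivery groups.
3. Beside the primary result, give a sensitivity table in which the intervention-arm variance is multiplied by 1 + (m − 1) × ICC for ICC 0.02, 0.05 and 0.10, with m the number analysed per group. A random group effect or a sandwich estimator clustered on delivery group is no substitute, because two groups cannot support either.
4. State as a limitation that the result rests on two delivery groups.

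No pass/fail ICC should be set. Any single value would be arbitrary and could not be checked in these data, so the whole range should be shown.

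The cost is one table from a variable the team should already hold. The downside is sensitivity intervals about 3% to 14% wider at 14 v 14, or about 6% to 28% wider at 28 v 28.

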**Fig. 2 Fig2:**
[figure not shown]
Basic process model of Self-Determination Theory developed for an intervention program. Source: adapted from Teixeira et al. [36]

The actions aimed to enhance participants’ awareness of their living conditions and health, delving into 24-h movement behaviors, especially physical activity, and their associations with depressive symptoms. As mentioned previously, all actions sought to implement techniques to support basic psychological needs and, in specific interventions, gamification strategies were employed. These strategies consist of mechanisms designed to motivate individuals to take action, aid in problem-solving, and facilitate learning [52]. This method has been used in educational programs [52] and coaching, demonstrating its efficacy in bringing about significant changes when integrated into daily life circumstances [53]. To this end, challenges/games were proposed, in which participants had to complete them until the subsequent meeting and present them to the person overseeing the dynamics. The psychology behind gamification seeks to stimulate learning, promote overcoming challenges, and motivate behaviors with the aim of recognizing those with better performance. It is important to highlight that this process must rely on voluntary participation, with all participants being aware of the rules and objectives of the task. Furthermore, the three components of the Unifying Theory of Physical Activity, developed and recently published by Matias and Piggin [54], were taken into account. The first component consists of the idea that physical activity/human movement is the result of inherent impulses, such as feeling, exploring, transforming and connecting, which “contribute to the meanings and purposes that sustain life and growth.” The intermediate level corresponds to the conditions/characteristics of physical activity, considering it as potential, distinct, and integrated. Finally, at the most external level, there are the social, political, and contextual qualities/forces that “interplay with the urges and shape human experience in/of physical activity” [54].

The main activities included (a) lectures covering various topics focused on the adoption and maintenance of healthy habits; (b) distribution of educational materials, including instruction manuals, addressing the necessary care individuals should take in their daily lives; (c) group discussions aimed at exploring the development and progress of the intervention; (d) practical activities involving the participation of family and friends; and (e) practical classes, such as yoga, capoeira, exergames, cycling, walking with pets, weight training, functional training, and gymnastics. The meetings followed a schedule with specific dates, times, and content, divided into four blocks, each consisting of eight sessions. The blocks were organized as follows: (a) contextualization, involving moments for the group to better acquaint themselves and dynamic activities addressing topics such as the relationship between depressive symptoms and 24-h movement behaviors; (b) adherence, providing general and specific guidelines on 24-h movement behaviors; (c) experimentation, offering participants more opportunities to engage in physical activity in different contexts and situations; and (d) maintenance, focusing on strategies and tools for maintaining healthy behaviors in both the short and long term.

Face-to-face meetings were conducted at the onset of each block, which represented 4 weeks of intervention, in order to establish a connection among participants and fostering discussions about their experiences during these periods. The face-to-face meetings took place at the premises of the Federal University of Santa Catarina and at locations suitable for engaging in physical activities. The remaining sessions were conducted via an online meeting platform. A WhatsApp group was also created to address inquiries, distribute support materials, and share photos, audios, and/or other resources related to the proposed activities, addressing other demands that emerged throughout the program. Tables 1, 2, 3, and 4 present the themes, objectives, support techniques for basic psychological needs, and the approaches/actions implemented in each meeting throughout the program, with each table corresponding to 1 month (4 weeks of intervention). In the supplementary material, it is possible to check the lesson plans for all 32 meetings of the Vincular Project, providing detailed information about the proposed content and dynamics.

**Table 1 Tab1:** Themes, objectives, dynamics carried out, explored psychological needs, and intervention strategies (week 1 to week 4)

Theme (references)	Objectives	Class dynamics	Take-home dynamics	Psychological needs	Intervention strategies for psychological needs
Meeting1: Introductory lesson □ [1]	To present the program schedule and meet the participants	- Presentation: the speaker throws a ball to a random person, who has to introduce themselves. The person who has just introduced themselves throws the ball to someone else, and so on	- Dynamics of similarities: in pairs or trios, the participants should talk with the aim of getting to know each other a little better and finding similarities and differences	Relatedness: involvement and connection	- Considering knowing the participants’ life story - Engaging actively in activities, including doing and playing together - Valuing group activities
Meeting 2: Depressive symptoms □ [2, 3]	To talk about depressive symptoms, their determinants and coping possibilities	- Report on the dynamics of similarities - "Breaking sedentary behavior". Participants stand in a circle. A rope is placed in the middle of the circle and some depressive symptoms are mentioned, as well as common situations among those who suffer from depressive symptoms. Those who perceive the symptoms and situations mentioned should approach the rope	- Do some physical activity of the participants’ own choosing	Autonomy: provision of justification Autonomy: orientation with intrinsic objective Competence: promotion of education	- Reflecting on reasons (internal and external) for adhering to the programs of physical activity - Tracing short-term goals - Providing educational material containing multidisciplinary information pertinent to the physical activity and health relationship
Meeting 3: Introduction to physical activity ○ [4, 5]	To explore the concept of physical activity, its benefits, domains, most practiced types and its relationship with depression	- Participants’ account of their chosen physical activity - "Do you practice physical activity?". Participants are asked to vote on whether they do any physical activity - "What are the benefits of physical activity?". Through an online platform, participants must report the benefits they know about the regular practice of physical activity and these will appear in a "word cloud" format	- Observe patterns of sedentary behavior and sleep (duration and quality)	Autonomy: language style Competence: provision of challenge	- Ensuring that the discourse is not mandatory, that ensures choice about what to do, such as different types of exercises, about how to adapt the activities - Situations that culminate in gamified processes
Meeting 4: Introduction to sedentary behavior and sleep ○ [3, 6]	To explore the concept of sedentary behavior, its harms, domains and most common types. Address the concept of sleep, its stages and sleep hygiene techniques	- Discussion on the patterns observed - "What can we do to break sedentary behavior?". Participants should list strategies or tips on how to reduce sedentary behavior - "How can we get a better quality of sleep?". Participants should list strategies or tips related to sleep hygiene	- Think about general questions related to physical activity and send them to the professors	Autonomy: language style Competence: provision of challenge	- Ensuring that the discourse is not mandatory, that ensures choice about what to do, such as different types of exercises, about how to adapt the activities - Situations that culminate in gamified processes
Meeting 5: Health-related physical fitness □ [7, 8]	To explore the elements of health-related physical fitness	Practice with different stations: - Warm-up: "10 passes" - Cardiorespiratory fitness: running and jumping jacks - Strength: squat and push-up - Agility: "boss sent" - Dynamic balance and coordination - Static balance - Flexibility	- For those who haven't done it yet, think about and list general doubts related to physical activity	Autonomy: structural facilitation Competence: provision of encouragement and support	- Adjusting the level of demand for the participants’ capacity to respond to the task - Adapting and building environmental alterations that ensure the beginning of the activity - Providing positive feedback to the class and individually, whether recognizing an effort of the participant or complimenting his attitude
Meeting 6: Barriers and facilitators to physical activity ○ [9]	To contribute to new reflections on the barriers and facilitators to physical activity	- Using the Mentimeter platform, identify the main barriers to physical activity perceived by the participants and discuss them, seeking to explore the frequency with which the barriers are perceived and the main reasons for this	- Family invitation: for the holiday, the participant should call a friend or family member to do some physical activity and send a record (audio, video, photo, text) about the experience	Competence: facilitation for completing processes relative to goals Relatedness: social support	- Different conditioning forms of achieving the goals - Encouraging the participant to invite friends and Family to carry out/participant in the programs of physical activity
Meeting 7: Curiosities about practicing physical activity ○	To propose a question and answer class on the world of physical activity. With all the questions sent in by the participants, the "Cards on the table" dynamic will be created. Each card has a question or a challenge, such as performing some physical activity. The participant must choose a number and, when the card is revealed, read it out loud to everyone. If the card chosen is a question, the participants can talk to each other in an attempt to answer the question together. If they don't know the answer, the teachers in charge help with the dynamic. If the letter chosen is a challenge, everyone should do it together		-	Autonomy: language style Competence: promotion of education	- Opting for language that ensures choice about what to do, such as different types of exercise, about how to adapt the activities - Providing educational material containing multidisciplinary information pertinent to the physical activity and health relationship
Meeting 8: Lecture with [name] □	To attend the lecture "Awaken the incredible in me"	- Conversation - Dance - Emotional support - Dynamics in pairs	- Reflection questions, such as why he is grateful for today, what he has learned this day, what he has done for others and what he has done for himself	Competence: provision of feedback	- Recognizing the improvement reached by the participant and remembering the “path” taken to reach it

□: face-to-face meetings; ○: online meetings; 1: Gillison et al. [37]; 2: Pearce et al. [10]; 3: Zhai, Zhang, Zhang [21]; 4: Nahas [55]; 5: Teychenne et al. [56]; 6: Hallgren et al. [57, 58]; 7: American College of Sports Medicine [59]; 8: Garber et al. [60]; 9: Rech et al. [61]

**Table 2 Tab2:** Themes, objectives, dynamics carried out, explored psychological needs, and intervention strategies (week 5 to week 8)

Theme (references)	Objectives	Class dynamics	Take-home dynamics	Psychological needs	Intervention strategies for psychological needs
Meeting 9: Conducting the intervention □ [1]	To discuss the experiences of the first month	- "Knot dynamics". The participants stand in a circle and memorize who is on their left and right side. To the sound of music, they walk freely around the room. When the teacher asks them to, they must stop where they are and hold hands with the people next to them, but without moving. The aim is to undo the knot and return to the starting position	- Fill in a list of routine activities in order to assess how they can better optimize their time and adopt new healthy behaviors in the short and long term	Competence: barriers acknowledge Relatedness: social support	- Recognizing the stages for behavior chances of each participant - Encouraging the group`s cohesion in the activities and resolution of problems
Meeting 10: Tools for 24-h movement patterns ○ [2–5]	To provide information on resources that help promote physical activity, reduce sedentary behavior and improve sleep quality	- Practicing physical activity and meditation through YouTube channels	- Choose two apps or another tool, try them out and report back on the experience. If possible, invite someone to practice together	Autonomy: provision of choice Relatedness: social support	- Favoring that the participant has and perceives option of choice in the conduction of all stages relative to the program of physical activity - Encouraging the participant to invite friends and Family to carry out/participant in the programs of physical activity
Meeting 11: *Exergames* □ [6–8]	To provide and explore a new tool for practicing physical activity, using all the elements of the body culture of movement	- Practice with Xbox 360: Just Dance, Kinect Sports	-	Relatedness: involvement and connection	- Engaging actively in activities, including doing and playing together
Meeting 12: Lecture with [name] □	To attend the lecture "Short and firm steps: an invitation to self-care with compassion"	- "Presentation dynamics". In order to value the individual for who they are and what they like, they must not define themselves from their professional life, but make a gentle and affectionate presentation, taking into account other aspects and spheres of life - "Dream list". A moment for each participant to reflect on their short-, medium- and long-term dreams	- "Box of happiness". The participant should list on a piece of paper various activities, things they like to do and that make them happy, cut out each one and keep them in a box. When they're having a bad day or realize they need to celebrate an achievement, they can open the box, take out a piece of paper and do what it says	Competence: facilitation for completing processes relative to goals	- Centering goals in the process - Valuing self-comparison as opposed to comparison with peers
Meeting 13: Environment, physical activity and their possibilities □ [9–12]	To explore and recognize a public space and discover the diversity of physical activity practices	- Recognizing space based on characteristics related to resources, conditions, access, aesthetics and safety - Human tic-tac-toe - Playing with a hula hoop - Steal tail - Flag-picking - Talking about collective vs. individual activities, outdoors vs. indoors, recreational vs. competitive, with vs. without supervision	- Recognizing the area in which they live (observing the place, the people who frequent it, what time of day it is busiest and what the built and perceived environment is like)	Autonomy: structural facilitation Autonomy: recognition of the participants’ perspective Competence: provision of challenges	- Recognizing the environmental potential for exercising by ensuring multiple potentials - Adapting and building environmental alterations that ensure the beginning of the activity - Considering participants’ reasons to exercise, such as preferences, expectations about health outcomes, and the cognitive and affective relationships established in the context of physical activity - Creates challenges to break the routine of the exercise sessions, whether for carrying out an exercise in a more challenging manner or carrying out activities in other environments
Meeting 14: Capoeira □ [13–16]	To learn about the history of capoeira, its institutionalization process and its main aspects, and practice it	- Practical initiation exercises - Activities with the basic elements and methodological aspects of capoeira teaching	-	Competence: provision of challenges Relatedness: Involvement and connection	- Creates challenges to break the routine of the exercise sessions, whether for carrying out an exercise in a more challenging manner or carrying out activities in other environments - Valuing group activities
Meeting 15: Les Mills □ [17–19]	To provide more vigorous forms of physical activity	- Power jump - Bodyattack	-	Autonomy: provision of choice	- Favoring that the participant has and perceives option of choice in the conduction of all stages relative to the program of physical activity
Meeting 16: Volleyball □ [20–22]	To propose a collective activity with the ball, recognizing and executing the main technical fundamentals of volleyball	- Warm-up games - Doubles exercises (set, bump, and ball control) - Mini court exercises - Game	-	Competence: provision of encouragement and support Relatedness: involvement and connection	- Providing positive feedback to the class and individually, whether recognizing an effort of the participant or complimenting his attitude - Valuing group activities

□: face-to-face meetings; ○: online meetings; 1: Gillison et al. [37]; 2: Aldenaini et al. [62]; 3: Pradal-Cano et al. [63]; 4: Rodríguez-González et al. [64]; 5: Silva et al. [65]; 6: Cugusi, Prosperini, Mura [66]; 7: Huang et al. [67]; 8: Li, Theng, Foo [68]; 9: Ferrari et al. [69]; 10: Kowitt et al. [70]; 11: Pontin et al. [71]; 12: Stappers et al. [72]; 13: Amitay [73]; 14: Delattre; Collaer [74]; 15: Jordan et al. [75]; 16: Martins et al. [76]; 17: Cunha [77]; 18: Jones et al. [78]; 19: Zureigat et al. [79]; 20: Guo et al. [80]; 21: Mohammadi [81]; 22: Vaccaro et al. [82]

**Table 3 Tab3:** Themes, objectives, dynamics carried out, explored psychological needs, and intervention strategies (week 9 to week 12)

Theme (references)	Objectives	Class dynamics	Take-home dynamics	Psychological needs	Intervention strategies for psychological needs
